**6.4.3.2. Definition of Non-Measurable Lesion Response Using RECIST Criteria**

- **Complete Response:** Complete disappearance of all *non-measurable* lesions.
- **Stable Disease:** A decrease or tumor stabilization of one or more *non-measurable* lesions. Subject with PR or CR that is not confirmed after at least 4 weeks are scored as SD unless they have new primary lesions.
- **Progressive Disease:** Progression of *non-measurable* lesion(s) (e.g., an increase in pleural effusions, or other fluid collections defined as an approximate doubling of the volume which was present at baseline or nadir, unless there is radiographic evidence of a benign cause for the fluid collection or the effusion is cytologically negative for malignant cells).

**6.4.3.3. Determination of Overall Response Using RECIST Criteria**

Overall Response (OR) is determined as the combination of assessments of *measurable* and *non-measurable* lesions using the following criteria:

| Measurable lesions | Non- measurable lesions | New lesions | Overall response |
|---------------------------|--------------------------------|--------------------|-------------------------|
| CR                 | CR                      | No          | CR               |
| CR                 | SD                      | No          | PR               |
| PR                 | SD                      | No          | PR               |
| SD                 | SD                      | No          | SD               |
| PD                 | any                     | Yes or No   | PD               |
| Any                | PD                      | Yes or No   | PD               |
| Any                | any                     | Yes         | PD               |

Best OR is the best confirmed response designation over the study as a whole, recorded between the date of first dose until the last tumor assessment for the individual patient in the study. The assessment of response at 12 weeks has particular emphasis due to the mechanism of action of ipilimumab inducing immune responses as basis for clinical responses. For the assessment of best OR, all available assessments per patient are considered. CR or PR determinations included in the best OR assessment must be confirmed by a second (confirmatory) evaluation meeting the criteria for response and performed no less than 4 weeks after the criteria for response are first met.

Imaging of the brain by MRT or CT, chest, abdomen and pelvis by CT scan is required at screening (ie, baseline) and at each tumor assessment visit in 12-week intervals, regardless of the location of known metastases. Similar methods of tumor assessment and similar techniques (CT or MRT) must be used to characterize each identified and reported lesion at screening and during subsequent tumor assessments. Imaging-based evaluation is preferred to clinical examination.

If progressive disease is assessed based only on a new lesion(s) found on bone scans, additional imaging studies of the lesion(s) should be performed to confirm the malignant nature of the new findings on the bone scan. Increased intensity of uptake in previously abnormal areas on bone scans is not considered progressive disease, unless the lesions seen on the correlative imaging studies performed of this area meet the criteria for progression. New areas of abnormal uptake on a bone scan represent progressive disease.

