**Secondary Endpoint (s)**

- All adverse events  $\geq$  Grade 3 according to CTCAE, Version 4.0 criteria, that are definitely, probably, or possibly related to the administration of the investigational agents will be assessed.
- Overall response rate (PR+CR) according to immune-related response Criteria (ir-RC) at any time in the study.
- Disease control rate irDCR (rate of CR or PR or SD) according to immune-related response Criteria (ir-RC) at any time in the study.
- Overall response rate (PR+CR) according to RECIST criteria at any time in the study.
- Disease control rate (CR or PR or SD) according to RECIST criteria at any time in the study.
- Progression free survival rate at 6 months, PFS is defined as the time from the first study treatment date until the first documented tumor progression date (as defined by immune related response criteria) or date of death, whichever occurs first.
- Overall survival
- Clinical efficacy parameter (1-year OS, ORR, DCR, PFS at 6 months) according to b-raf mutational status of tumor (b-raf V600E yes versus no), brain metastases, LDH and HLA-A2

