Consistent with the known mechanism of action of ipilimumab, the reduction in tumor burden in the 3 primary melanoma studies was characterized by novel patterns of measurable clinical effect. In addition to objective response (complete response [CR] and partial response [PR]), and SD as measured by mWHO, novel patterns of clinical activity, which are related to the immunological mechanism of action of ipilimumab, were reported in all 3 studies. These patterns of activity were characterized by overall reductions from baseline in total tumor burden (index plus measurable new lesions, when present) after the appearance of new lesions and/or after an initial tumor burden increase. Of 227 treated subjects who received 10 mg/kg ipilimumab in studies CA184022 and CA184008, 9.7% of subjects demonstrated disease control after an initial increase in tumor burden and/or appearance of new lesions

(Wolchok et al., 2010; O'Day et al., Ann Oncol 2010; CA184022 Clinical Study Report 2008; CA184008 Clinical Study Report, 2008; CA184007 Clinical Study Report 2008).

Survival data from these 3 primary studies (CA184022, CA184008, and CA184007) are supported by OS data from CA184004 and MDX-010-28. Both studies enrolled previously untreated and pretreated subjects with advanced melanoma. In CA184004, 42 subjects were randomized to 10 mg/kg ipilimumab. The median follow-up for survival in this study was 8.6 months. The median OS was 11.8 months (95% CI: 6.1, --); the 1-year survival rate was 44.2% (95% CI: 24.1%, 64.1%) (CA184004 Clinical Study Report, 2008). Data are available for 23 response-evaluable subjects treated at 10 mg/kg ipilimumab in MDX010-15 who enrolled in the follow-up study MDX010-28. The median follow-up for survival in this study was 13.4 months. The median OS was 13.2 months (95% CI: 9.4, 19.4). The overall survival for 2 subjects with ongoing responses was 26.0+ months and 25.0+ months (MDX010-19 Clinical Study Report, 2007).

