#### **6.4.3. Evaluation of Tumor Response Using RECIST Criteria**

##### **6.4.3.1. Definition of Measurable Lesion Response Using RECIST Criteria**

Measurable lesion will be measured in a dimension using the longest diameter is used. The tumour response will be investigated during every re-staging visit.

Complete response (CR): Disappearance of all lesions and appearance of no new lesions.

Partial response (PR): At least a 30% decrease in the sum of the longest diameter of measurable lesions. No new lesions may occur or individual lesions progress.

Progressive disease (PD): At least a 20% increase in the total of the longest diameters of measurable lesions (as reference to the smallest sum recorded since the treatment started) or the appearance of new lesions.

If the measurable lesion disappears and the progression of a lesion or the appearance of new lesions is observed elsewhere at the same time, this is also documented as a progressive disease.

Stable disease (SD): Neither a partial nor a complete response in the absence of progression.

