#### 6.4.4.5. Immune-Related Best Overall Response Using irRC (irBOR)

irBOR is the best confirmed irRC overall response over the study as a whole, recorded between the date of first dose until the last tumor assessment before subsequent therapy (except for local palliative radiotherapy for painful bone lesions) for the individual subject in the study. For the assessment of irBOR, all available assessments per subject are considered.

irCR or irPR determinations included in the irBOR assessment must be confirmed by a second (confirmatory) evaluation meeting the criteria for response and performed no less than 4 weeks after the criteria for response are first met.

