**Best Overall Response**

- Best response during therapy prior to PD

| Target lesion | Non target lesion | OR |
|----------------------|--------------------------|-----------|
| CR                   | CR                       | CR        |
| CR                   | SD / IR                  | PR        |
| PR                   | No PD                    | PR        |
| SD                   | No PD                    | SD        |
| PD                   | –                        | PD        |
| –                    | PD                       | PD        |
| –                    | New lesion               | PD        |
| New lesion           | -                        | PD        |

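### RECIST best response is defined in two incompatible ways: over the whole study in 6.4.3.3 but only up to PD in Appendix 9, with different rules for growth of a single lesion

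*Protocol*

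**What the plan says.** **Window.** Section 6.4.3.3 states: "Best OR is the best confirmed response designation over the study as a whole". It runs from first dose to the patient's last tumour assessment and adds: "For the assessment of best OR, all available assessments per patient are considered". The synopsis lists the secondary endpoint in the same sense: "Overall response rate (PR+CR) according to RECIST criteria at any time in the study"; RECIST DCR is worded likewise. Appendix 9, in its table for best overall response, says: "Best response during therapy prior to PD". For irRC, Section 6.4.4.5 ends the window at a defined point: "until the last tumor assessment before subsequent therapy". Section 6.4.3.3 has no such limit for RECIST.

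**Growth of a single lesion.** Section 6.4.3.1 attaches a condition to PR: "No new lesions may occur or individual lesions progress". It scores PD in one further situation: "If the measurable lesion disappears and the progression of a lesion or the appearance of new lesions is observed elsewhere at the same time". Appendix 9 gives PR for a fall of at least 30% in the sum of longest diameters, provided there is no non-target PD and no new lesion. It has no condition on individual target lesions.

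**Use.** Sections 9.3.2 and 9.5 report RECIST OR and DCR with exact 95% confidence intervals in the Response-evaluable population.

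**The concern.** The same scans can give different RECIST best responses depending on which text is applied, and the protocol does not say which governs. Up to 26 sites are planned, so both readings could be in use.

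The whole-study rule also weakens the purpose of reporting two criteria. Section 1.3.7 justifies irRC because conventional criteria miss benefit that appears after apparent progression. If responses after RECIST PD may count as RECIST responses, the comparison between the two sets of rates is blurred. The asymmetry with 6.4.4.5 adds to this: as written, the conventional criterion has no cut at subsequent therapy, while the immune-related one does.

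**Working it through.** **1. Do scans after RECIST PD exist?** Yes, within limits.
- Section 5.1 asks for assessments at weeks 12, 24, 36 and 48 in all patients who start induction. Those with clinical progression during induction follow standard of care instead.
- Section 6.1.1 follows patients who stop ipilimumab until irPD. Under 6.4.4.3 new lesions alone are not irPD, so irPD can come later than RECIST PD.
- Section 6.1.1.3 continues 12-weekly imaging through re-induction, which is given only after progression (Section 5.2).
- Against this, Section 6.1.1 ends re-staging after documented progression in patients not eligible for re-induction. Patients who progress and switch treatment are followed only for date of death.

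**2. The two texts applied to the same patient.**

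| Course under RECIST | 6.4.3 | Appendix 9 | Endpoint affected |
|---|---|---|---|
| SD, then PD, then confirmed PR on re-induction | PR | SD | ORR |
| PD at first assessment from target growth, then shrinkage to confirmed PR, if scanned again | PR | PD | ORR and DCR |
| Sum falls 40%, one target lesion progresses, no non-target PD, no new lesion | not PR: SD or PD | PR | ORR; DCR only if scored PD |
| One measurable lesion disappears, another target progresses, sum down at least 30%, no new lesion | PD | PR | ORR and DCR |

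The DCR column uses the synopsis definition (CR, PR or SD). Section 9.3.2 defines RECIST DCR as a best response of PR or CR, which read literally makes it the same as ORR.

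**3. Direction.** Rows 1 and 2 raise ORR under 6.4.3 relative to Appendix 9. Rows 3 and 4 lower it. The net sign is not known.

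**4. Size.** The only related figure in the protocol is in Section 1.3.6: "9.7% of subjects demonstrated disease control after an initial increase in tumor burden and/or appearance of new lesions". Section 1.3.7 gives the count.
- Reproduced: 22/227 = 0.0969, or 9.7%; exact (Clopper-Pearson) 95% CI 6.2% to 14.3%.
- Let f be the assumed share of that group who would be PD under Appendix 9 but would gain a RECIST best response of SD or better under the whole-study window. DCR shift = f × 9.69 points; patients = f × 0.0969 × 200.

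| f | DCR shift (points) | Patients of 200 |
|---|---|---|
| 0 | 0 | 0 |
| 0.25 | 2.4 | 4.8 |
| 0.5 | 4.8 | 9.7 |
| 0.75 | 7.3 | 14.5 |
| 1 | 9.7 | 19.4 |

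The denominator for DCR is the Response-evaluable population, whose size is not given. With an assumed 150 evaluable patients, f = 1 means 14.5 patients and the same 9.7 points.

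**5. Why this is not an estimate.** The 9.7% compares irRC with mWHO, at 10 mg/kg, in earlier trials. It includes stable disease, so it says nothing specific about ORR. It also includes patients with persisting new lesions, whom the 6.4.3.3 table scores as PD at that assessment.

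**The case against.** The strongest reply is that the governing text can be identified. Section 9.3.2 refers RECIST OR and DCR to a section number that is evidently 6.4.3.3 with the numbering off by one. The synopsis agrees with 6.4.3.3, and neither Section 6.4 nor Section 9 points to the RECIST appendix. Section 6.4.5 gives a reason for looking late. On this view Appendix 9 is a stray summary. That probably settles which window was meant. It does not remove the contradiction, and it leaves the body rule counting responses after PD as RECIST responses, when the irRC endpoints already serve the late-response rationale.

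Second, the effect is limited. Patients who switch treatment after progression are not formally scanned, and non-study anticancer agents are prohibited during the study, so responses after another drug should be few. Re-induction requires earlier stable disease or response, so patients with RECIST SD or better before PD already count in DCR. All non-primary analyses are exploratory under Section 9.5. These points stand and limit the importance of the finding.

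Third, a reader might infer that a new lesion at week 12 followed by a confirmed PR at weeks 24 and 36 always separates the two texts. It does so only if the new lesion has resolved or is no longer counted as new. Otherwise 6.4.3.1 and the 6.4.3.3 table withhold PR as well.

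**Conclusion.** Both contradictions are in the current text, and each can change a patient's RECIST best response and so the secondary endpoints ORR and DCR. The clearest case needs no borrowed figure: SD, PD, then confirmed PR on re-induction.

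A reader might infer that RECIST ORR and DCR differ by up to about 10 points between the texts, or that the RECIST rates are inflated overall. The protocol supports neither. Reaching 9.7 points needs f = 1 and a transfer from irRC/mWHO at 10 mg/kg to RECIST at 3 mg/kg. That figure concerns the window effect on DCR only and gives no bound for ORR. The single-lesion rule works the other way on ORR, and no rate for it is given. The net effect on either endpoint cannot be derived from the protocol.

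One-year survival, the primary endpoint, and the sample size do not depend on this point. It should be corrected, but it does not threaten the trial's main result.

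**What to change.** - In 6.4.3.3, define RECIST best response as the best confirmed response from first dose to the first RECIST PD or the start of subsequent anticancer therapy, whichever is first. Report later responses under irRC only.
- Reword the synopsis RECIST endpoints, which now cover the whole study, and the window line in Appendix 9 to match. Changing 6.4.3.3 alone would create a new conflict with the synopsis.
- State one rule for growth of a single lesion within a shrinking sum, identically in 6.4.3.1 and Appendix 9. If the individual-lesion condition is kept, say what counts as progression of one lesion, which 6.4.3.1 does not define.
- In 9.3.2, correct the RECIST DCR definition to CR, PR or SD, as in the synopsis, and repair the cross-references.

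The cost is wording only, with the same scans and visits. RECIST ORR and DCR may come out slightly lower than under the present 6.4.3.3 window.

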#### **6.4.4. Definition of Tumor Response Using irRC**

The sum of the products of diameters at tumor assessment using the immune-related response criteria (irRC) for progressive disease incorporates the contribution of new measurable lesions. Each net Percentage Change in Tumor Burden per assessment using irRC criteria accounts for the size and growth kinetics of both old and new lesions as they appear.

##### **6.4.4.1. Definition of Index Lesions Response Using irRC**

- **irComplete Response (irCR):** Complete disappearance of all *index* lesions. This category encompasses exactly the same subjects as “CR” by the mWHO criteria.
- **irPartial Response (irPR):** Decrease, relative to baseline, of 50% or greater in the sum of the products of the two largest perpendicular diameters of all *index* and all new measurable lesions (i.e., Percentage Change in Tumor Burden). Note: the appearance of new measurable lesions is factored into the overall tumor burden, but does not automatically qualify as progressive disease until the SPD increases by  $\geq 25\%$  when compared to SPD at nadir.
- **irStable Disease (irSD):** Does not meet criteria for irCR or irPR, in the absence of progressive disease.
- **irProgressive Disease (irPD):** At least 25% increase Percentage Change in Tumor Burden (i.e., taking sum of the products of all *index* lesions and any new lesions) when compared to SPD at nadir.

##### **6.4.4.2. Definition of Non-Index Lesions Response Using irRC**

- **irComplete Response (irCR):** Complete disappearance of all *non-index* lesions. This category encompasses exactly the same subjects as “CR” by the mWHO criteria.
- **irPartial Response (irPR) or irStable Disease (irSD):** *non-index* lesion(s) are not considered in the definition of PR, these terms do not apply.
- **irProgressive Disease (irPD):** Increases in number or size of *non-index* lesion(s) does not constitute progressive disease unless/until the Percentage Change in Tumor Burden increases by 25% (i.e., the SPD at nadir of the index lesions increases by the required amount).

#### 6.4.4.3. **Impact of New Lesions on irRC**

New lesions in and by themselves do not qualify as progressive disease. However their contribution to total tumor burden is included in the SPD which in turn feeds into the irRC criteria for tumor response. Therefore, new non-measurable lesions will not discontinue any subject from the study.

#### 6.4.4.4. **Definition of Overall Response Using irRC**

Overall response using irRC will be based on these criteria:

- **Immune-Related Complete Response (irCR):** Complete disappearance of *all* tumor lesions (index and nonindex together with no new measurable/unmeasurable lesions) for at least 4 weeks from the date of documentation of complete response.
- **Immune-Related Partial Response (irPR):** The sum of the products of the two largest perpendicular diameters of all index lesions is measured and captured as the SPD baseline. At each subsequent tumor assessment, the sum of the products of the two largest perpendicular diameters of all index lesions and of new measurable lesions are added together to provide the Immune Response Sum of Product Diameters (irSPD). A decrease, relative to baseline of the irSPD compared to the previous SPD baseline, of 50% or greater is considered an immune Partial Response (irPR).
- **Immune-Related Stable Disease (irSD):** irSD is defined as the failure to meet criteria for immune complete response or immune partial response, in the absence of progressive disease.
- **Immune-Related Progressive Disease (irPD):** It is recommended in difficult cases to confirm PD by serial imaging. Any of the following will constitute progressive disease:
  - At least 25% increase in the sum of the products of all index lesions over baseline SPD calculated for the index lesions.
  - At least a 25% increase in the sum of the products of all index lesions and new measurable lesions (irSPD) over the baseline SPD calculated for the index lesions.

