**Examinations:**

The disease will be assessed at baseline, at week 12 and for patients with stable disease or better responses, thereafter every 12 weeks in the absence of PD with a maximum of one year after receive of the first treatment. Response evaluation will be done according to immune-related response criteria (Wolchok et al., CCR 2009).

All patients who prematurely discontinued treatment due to a drug-related adverse event prior to Week 12 (in the absence of disease progression) will return for all study visits and procedures including Week 12 and, if appropriate, further re-staging assessments. Any patient with documented progression at any scheduled re-staging visit and who will not receive any re-induction will undergo no further re-staging visits.

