## 5 STUDY THERAPY WITH IPILIMUMAB

### 5.1 Induction Treatment

Subjects enrolled after IC will receive ipilimumab according to the protocol of the completed Medarex study MDX010-20 (Hodi et al., NEJM, 2010) as a single agent at a dose of 3mg/kg for 4 times over 10 weeks (1 cycle): The day subjects receive the first dose of protocol ipilimumab therapy will define Day 1. Ipilimumab, 3 mg/kg, day 1 (W1), 22 (W4), 43 (W7), 64 (W10) must be administered intravenously over a 90-minute period every 3 weeks for a total of four doses, as tolerated. This dose demonstrated an overall survival benefit for the first time in treating metastatic melanoma in a controlled randomized clinical study (Hodi et al., NEJM, 2010).

- Electrocardiogram (ECG) examination should be performed during screening and week 12. Patients with an existing myocarditis are excluded from this study. For patients with suspicion of myocarditis e.g. dyspnoea, functional insufficiency etc. ECG examinations have to be performed before each treatment.
- Laboratory evaluations should be performed (refer to section 6.1.1.2) and the results examined before administration of each ipilimumab dose.
- As durable disease stabilization and/or objective tumor response can be seen after early progression before Week 12, it is recommended that, in the absence of dose-limiting toxicities (eg, serious irAEs), all four doses of ipilimumab be administered over the initial 12 weeks even in the setting of apparent clinical progression, providing the subject's performance status remains stable.
- All subjects who enter the induction period, including those who may have discontinued treatment for drug-related AEs should obtain a 12-week, 24-week 36-week and 48 week tumor assessment. Those patients who have evidence of clinical progression during the induction period, should obtain further tumor assessment according to Standard of Care.
- Based on clinical experience in the ongoing and completed melanoma studies, the following recommendations apply for subject management in light of the Week 12 or later tumor assessments:
  - The appearance of new lesions in subjects with other stable or shrinking baseline tumor burden may be experiencing clinical benefit and should continue in follow-up before alternative anti-cancer agents are considered. These subjects can be seen to have continued tumor shrinkage in follow-up scans.

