### 5.5.3 Discontinuation of Study Therapy

Subjects MUST be discontinued from study therapy AND/ OR withdrawn from the study for the following reasons:

- Withdrawal of informed consent (subject's decision to withdraw for any reason)
- Any clinical adverse event, laboratory abnormality or intercurrent illness which, in the opinion of the investigator, indicates that continued treatment with study therapy is not in the best interest of the subject
- Clinical deterioration of subject's condition such that further benefit from ipilimumab dosing is unlikely or requires a change of therapy
- The development of progression (PD) in the global tumor burden (progression must be confirmed by serial imaging 4-6 weeks later)
- Pregnancy
  - All WOCBP should be instructed to contact the investigator immediately if they suspect they might be pregnant (e.g., missed or late menstrual period) at any time during study participation. Institutional policy and local regulations should determine the frequency of on study pregnancy tests for WOCBP enrolled in the study.
  - The investigator must immediately notify the coordinating investigator in the event of a confirmed pregnancy in a patient participating in the study.
- Termination of the study
- The compulsory detention for treatment of either a psychiatric or physical (e.g., infectious disease) illness

If study drug administration is discontinued, the reason for discontinuation will be recorded.

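### Immune-related progression is measured from nadir in 6.4.4.1 and 6.4.4.2 but from baseline in 6.4.4.4, so irPFS has no single event date for patients who shrink and then regrow

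*Protocol*

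**What the plan says.** **Reference for irPD.** Section 6.4.4.1 defines irPD by a 25% rise in the burden of index plus new lesions "when compared to SPD at nadir", and repeats that reference in its note under irPR. Section 6.4.4.2, on non-index lesions, points the same way: "the SPD at nadir of the index lesions increases by the required amount". Section 6.4.4.4 gives two irPD criteria, one for index lesions alone and one that adds new measurable lesions. Both are tied to baseline; the second reads "At least a 25% increase in the sum of the products of all index lesions and new measurable lesions (irSPD) over the baseline SPD".

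**The irRC table after 6.4.4.4** (Table 3, a number also used for a safety table in 1.3.5.b) has one percent-change column with no stated reference. In the partial-response and stable-disease rows, irSD ends below +25% and irPD begins above +25%. In the progressive-disease row, irPD begins at +25%.

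**Endpoints.** PFS runs from first dose to first documented irRC progression or death (synopsis, 9.3.2, 9.5). Section 9.5 reports the 6-month rate and the median. irDCR rests on the best overall irRC response (9.3.2). The primary endpoint is 1-year survival, and 9.5 labels all other analyses exploratory.

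**Neighbouring texts.** On confirmation, 6.4.4.4 says "It is recommended in difficult cases to confirm PD by serial imaging", while 5.5.3 says "progression must be confirmed by serial imaging 4-6 weeks later". On scanning, the synopsis says "Any patient with documented progression at any scheduled re-staging visit and who will not receive any re-induction will undergo no further re-staging visits", while 5.1 says that all who enter induction "should obtain a 12-week, 24-week 36-week and 48 week tumor assessment".

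**The concern.** A progression endpoint needs one trigger. Here the trigger depends on which subsection the site or programmer follows, and the two diverge only after shrinkage, in the patients who first benefited. Under the baseline rule such a patient can regrow far beyond 25% from nadir without an event; under the nadir rule the same scan is an event. With scans 12 weeks apart, the irPFS date can move by one or more visits. An analysis plan could choose one derivation, but it could not make progression calls consistent across sites once they have been made under different rules.

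**Working it through.** The protocol states no figure that depends on this definition, so there is nothing to reproduce. The check applies both rules to the same tumour-burden paths.

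**Inputs.** Baseline burden = 100. N = lowest value so far, baseline included. The threshold is a 25% rise (6.4.4.1, 6.4.4.4). Scans are at weeks 12, 24, 36 and 48 (5.1).

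**Triggers.** Nadir rule: 1.25 × N. Baseline rule: 1.25 × 100 = 125. Regrowth from nadir that the baseline rule needs: 125/N − 1.

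| Nadir N | Trigger, nadir rule | Trigger, baseline rule | Regrowth needed, baseline rule |
|---|---|---|---|
| 90 | 112.5 | 125 | 39% |
| 80 | 100 | 125 | 56% |
| 60 | 75 | 125 | 108% |
| 50 | 62.5 | 125 | 150% |
| 30 | 37.5 | 125 | 317% |

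**Paths.**
- 100 → 60 → 80: 80/60 = 1.33, so +33% and irPD by nadir; 80/100 gives −20% and irSD by baseline.
- 100 → 40 → 60: +50% and irPD by nadir; −40% and irSD by baseline.
- 100 → 30 → 60: +100% and irPD by nadir; −40% and irSD by baseline.

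**When the date differs.** A visit is classified differently only if burden is at least 1.25 × N and still below 125. At week 12 the nadir is still baseline, so the rules agree. Of the two scans scheduled within six months (weeks 12 and 24), only week 24 can therefore differ: the patient must shrink by week 12 and regrow at least 25% from nadir by week 24 while staying below 125.

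**irDCR.** A nadir below baseline means that some earlier scan was already irSD or better under both rules. With no shrinkage the two triggers coincide. The reference alone therefore cannot change irDCR.

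**Logic check.** Fourteen burden values from 10 to 150 at each of four scans give 14⁴ = 38,416 paths, with irPD given precedence when a scan meets two categories. The first irPD date differed in 16,795 paths, irPD status by week 24 in 8,428, and irDCR in 0. The grid is an assumption, and these counts are not patient proportions.

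**Effect on the rate.** With 200 patients, 2 reclassified move the 6-month rate by 2/200 = 1 percentage point, and 10 move it by 5 points. The documents do not allow the number affected to be estimated.

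**The case against.** **Lesion level versus overall response.** One could say that 6.4.4.1 grades index lesions and 6.4.4.4 alone grades the patient. That fails, because 6.4.4.1 already counts new lesions ("lesions and any new lesions) when compared to SPD at nadir"), the same quantity as irSPD. Nor does the table rescue it: with its column read against baseline, index progression by the nadir rule at −40% fits no row.

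**Importance.** The endpoints concerned are secondary and exploratory, and no test, sample size or decision rests on them. This stands and limits the severity. It is also true that the gap is small after slight shrinkage (112.5 against 125 at a nadir of 90), and that a jump to 130 is irPD at the same visit under both rules.

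**Stronger readings that a reader might infer, and why they do not hold.**
- *The confirmation texts leave irPFS undefined.* Section 5.5.3 governs stopping therapy, and the synopsis and Appendix 8 govern re-induction. The PFS definitions date the event at first documented irPD, and 6.4.4.5 asks for confirmation only of irCR and irPR.
- *Late responses are lost, at a rate of 9.7%.* That figure (22/227, section 1.3.7) is disease control at or after mWHO progression at 10 mg/kg. irRC adds new lesions to total burden, so many such patients need not reach irPD, and this trial uses 3 mg/kg.
- *The stop rule contradicts 6.4.5.* Section 6.4.5 concerns increases in the first 12 weeks, while the stop rule applies at scheduled restaging, which starts at week 12. Section 5.1 also sends patients with clinical progression during induction to standard-of-care imaging.
- *Confirmed irPD could be required at no cost.* The visit schedule has no 4-to-6-week confirmatory scan.

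What remains of the neighbouring texts is that they are not aligned with each other.

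**Conclusion.** The contradiction is real and stands in the current text. For patients who shrink and then regrow, irPD status and date can depend on the subsection followed: the trigger is 75% or 125% of baseline after a nadir of 60%, and 37.5% or 125% after a nadir of 30%. The 6-month irPFS rate and median irPFS are therefore not uniquely defined. The thresholds follow exactly from the two rules; the number of patients affected is unknown.

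A reader might also infer that irDCR depends on the reference point; it does not. The primary 1-year survival endpoint is unaffected. Because the affected endpoints are secondary and exploratory, this should be fixed but is not a critical defect.

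**What to change.** For the irRC endpoints, use one reference throughout:

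- In both irPD bullets of 6.4.4.4, replace baseline with *SPD at nadir (baseline included)*. This agrees with 6.4.4.1 and 6.4.4.2, and with the smallest-sum rule already used for RECIST in 6.4.3.1 and Appendix 9.
- In the irRC table, state the references (baseline for the −50% cut, nadir for the +25% cut) and use at least 25% in every irPD row. Add that irPD takes precedence, since a scan can then meet both cuts: 100 → 30 → 40 is −60% from baseline and +33% from nadir.
- Keep the irPFS event at first documented irPD, as the PFS definition already says.
- Reconcile with this definition the passages on confirming progression and on when restaging ends (synopsis, 5.1, 5.5.3, 6.1.1, 6.4.4.4, Appendix 8). No treatment-stopping or re-induction rule is proposed here.

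The cost of aligning the reference and the table is a short wording amendment and one derivation rule, with no added scans. The downside is that irPFS may be somewhat shorter in patients who first shrank.
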